## Abstract

**Background:**

More than half of the world’s population lives in Asia. With current life expectancies in Asian countries, the burden of cardiovascular disease is increasing exponentially. Overcrowding in the emergency departments (ED) has become a public health problem. Since 2015, the European Society of Cardiology recommends the use of a 0/1-h algorithm based on high-sensitivity cardiac troponin (hs-cTn) for rapid triage of patients with suspected non-ST elevation acute coronary syndrome (NSTE-ACS). However, these algorithms are currently not recommended by Asian guidelines due to the lack of suitable data.

**Methods:**

The DROP-Asian ACS is a prospective, stepped wedge, cluster-randomized trial enrolling 4260 participants presenting with chest pain to the ED of 12 acute care hospitals in five Asian countries (UMIN; 000042461). Consecutive patients presenting with suspected acute coronary syndrome between July 2021 and Apr 2024 were included. Initially, all clusters will apply “usual care” according to local standard operating procedures including hs-cTnT but not the 0/1-h algorithm. The primary outcome is the incidence of major adverse cardiac events (MACE), the composite of all-cause death, myocardial infarction, unstable angina, or unplanned revascularization within 30 days. The difference in MACE (with one-sided 95% CI) was estimated to evaluate non-inferiority. The non-inferiority margin was prespecified at 1.5%. Secondary efficacy outcomes include costs for healthcare resources and duration of stay in ED.

**Conclusions:**

This study provides important evidence concerning the safety and efficacy of the 0/1-h algorithm in Asian countries and may help to reduce congestion of the ED as well as medical costs.

## Introduction

Emergency department (ED) overcrowding is a major public health problem in Asian countries and has been associated with poor outcomes, increased resource use, and restricted access to care [1–3]. Chest pain is one of the most frequent reasons for emergency department (ED) visits. These patients are frequently managed in the ED to rule out an acute coronary syndrome (ACS). However, ACS is diagnosed only in a minority (about 5–20%, depending on the clinical setting) while the vast majority does not suffer from a life-threatening cause of chest pain [4]. As a consequence, a large number of patients are managed in the hospital inappropriately [5]. This practice produces an increase in costs and overcrowds the ED, with a negative impact on the patients and the healthcare system. Waiting times are a pressing societal problem and efficient treatment pathways, which are essential to ensure the accurate, timely, and cost-effective early management of ACS patients. Conversely, missed diagnosis and treatment inefficiency are associated with increase morbidity, mortality, and costs [6, 7].

Based on the above, efficient patient stratification approaches are needed. The population composition and economic environment varies widely in a given population, so such stratification approaches should be kept as simple as possible. The European Society of Cardiology (ESC) guidelines recommend the use of high-sensitivity cardiac troponin (hs-cTn) 0-h/1-h algorithms in patients presenting with suspected non-ST elevation ACS (NSTE-ACS) as Class I, Level B since 2015 [8, 9]. This algorithm was based on conceptual considerations given the ongoing clinical implementation of hs-cTn assays at that time and was initially supported only by limited data [10]. Due to the lack of data from Asian countries, which differ substantially from Central European countries regarding patient’s characteristics and healthcare systems, the 0/1-h algorithm is not recommended by Asian guidelines [11–13]. Accordingly, most patients presenting with suspected ACS in Asian countries are still assessed with serial retesting of hs-cTn after 2, 3, or even 6 h, which is not only more time consuming, but has been described to be less safe in comparison to the ESC 0/1-h algorithm [14].

The “*d*iagnosis and *r*eduction of *o*vercrowding emergency de*p*artment in *Asia*n *a*cute *c*oronary *s*yndrome based on the 0-1 algorithm using high-sensitivity troponin T assay” (DROP-Asian ACS) study is a stepped wedge, cluster-randomized trial, which is currently being conducted to compare the real-world safety and efficacy of the usual care with the 0/1-h algorithm in patients with suspected non-ST elevation ACS (NSTE-ACS) (UMIN; 000042461). The findings will help to clarify how to safely reduce ED dwelling time and medical costs in order to achieve the most efficient level of care for patients in the ED.

## Methods

### Follow-up and clinical end endpoints

After hospital discharge, patients were contacted after 30 days by telephone calls or appointments.

#### Primary outcome measure

The primary aim of the present study is to determine the relative safety of the 0/1-h algorithm compared with the current standard of care for patients presenting with suspected NSTE-ACS to the ED. Primary outcome measure is the incidence of major adverse cardiac events (MACE), defined as the composite of cardiovascular death, new acute myocardial infarction (AMI) (type 1 or 2), unstable angina, or unexpected revascularization within 30 days (defined as any unplanned hospitalization with cardiac revascularization performed within the first 12 h after hospital admission in the context of ACS). Of note, AMI diagnosed within 12 h of index presentation among participants continuously in-hospital will be considered as the index presenting AMI and not included as an endpoint event. An AMI documented to have commenced outside this time (recurrent/new AMI type 1 or 2) in hospitalized patients or within 12 h of index presentation among participants already discharged from the hospital (missed AMI type 1 or 2) will be considered an endpoint event.

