#### Secondary outcome measures

The following predefined secondary outcomes are considered:The proportion of patients managed as outpatients in order to quantify the efficacy of the investigated approaches in both arms.The time from ED presentation to discharge in outpatients. The ED dwell time is derived from a common electronic patient record system used across all participating sites and is calculated as the time of the medical examination between the start time (sign-in time: defined as first medical contact with a MD or the triage nurse) and the end time (sign-off time: defined as the time when the attending physician has finished all medical procedures in the ED, including charting, with the patient to ready to leave the examination room either to be discharged or transferred to a different unit/ward within the hospital).All-cause mortality (cardiovascular death and non-cardiovascular death) and new myocardial infarction (type 1 or 2) within 30 days after the index presentation.Incidence of any cardiac revascularization within 30 days after the index presentation.Incidence of ED representation or hospitalization for unstable angina within 30 days after the index presentation.Costs for healthcare resource use within 30 days following the index ED presentation are calculated based on each country’s guidelines and cost tables for hospitals. Different costs are used for academic and general hospitals. For each patient, the costs are calculated based on the observed number and type of healthcare resources used.Incidence of cardiac examinations (e.g., stress testing or coronary angiography) within 30 days after the index presentation. Adherence to the intervention condition (the 0/1-h algorithm) was evaluated.

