### The adjudicated final diagnosis

Both components of the primary outcome are adjudicated by two independent cardiologists. Interrater reliability is assessed by documenting the number of patients with mismatch in the final diagnosis of AMI by the 2 adjudicating cardiologists, which requires involvement of a third cardiologist. AMI will be defined according to the Fourth Universal Definition of Myocardial Infarction, which requires evidence of myocardial necrosis in addition to ischemia (as shown through ECG changes, positive findings of stress ECG, myocardial perfusion, coronary CTA or CAG) [25]. In brief, necrosis will be diagnosed based on an increase or decrease (20% relative increase) in the hs-cTnT concentration with at least 1 measurement above the 99th percentile of the normal reference range at a level of assay imprecision near 10%. Type I MI is characterized by atherosclerotic plaque rupture, ulceration, erosion, or dissection, with the resulting intraluminal thrombus in one or more coronary arteries leading to myocardial necrosis (any hs-cTnT concentration above 14 ng/L, with an increase and decrease in the hs-cTnT concentration where serial testing is available). Type II MI is defined as myocardial necrosis in which a condition other than coronary plaque instability contributed to an imbalance between the myocardial oxygen supply and demand (e.g., coronary artery spasm, coronary embolisms, hypertension, or hypotension). All other patients will be classified as “no AMI” in this analysis. Unstable angina will be diagnosed in patients with typical ischemic symptoms at rest or minor exercise with no evidence of acute myocardial necrosis (normal or elevated hs-cTnT levels without any relevant change during serial sampling). Vasospastic angina pectoris was diagnosed in patients with no obvious coronary stenosis, in which an ECG revealed ST elevation, or there was angiographic evidence of a coronary artery spasm that was released after the intracoronary administration of 1 mg of nitroglycerin [18, 26, 27]. Noncardiac chest pain was diagnosed based on the absence of findings from laboratory tests, ECG, and chest radiography at the 30-day follow-up.

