### Study governance

The steering committee of emergency physicians, emergency and cardiology nurses, cardiologists, implementation experts, and clinical pathologists with representation from each of the participating hospitals is providing oversight to the study. Data management is centralized at Novelle PACE Inc. (Tokyo, Japan). REDCap (Research Electronic Data Capture) will be used as electronic case report form (eCRF) to collect and manage study data. All local and server databases will be secured with password-protected access systems, access logging, and encryption. Members of the endpoint committee have access to the patient information via encrypted server access and encrypted hard drives. A clinical event adjudication committee, independent of the study management team, is providing blinded evaluations (events deidentified for treatment arm, hospital, and patient details) of all components of the primary endpoint, including index (within 12 h of initial presentation) and subsequent MI. All study-related information will, until collection, be stored securely at the study sites in areas with limited access. After collection and entry, laboratory specimens, reports, and data collection forms will be identified by a coded participant ID number to maintain participant confidentiality. Forms and any other listings that link participant ID numbers to other identifying information will be stored separately from study records with the participant ID number.

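### The primary endpoint excludes the index event for AMI only, so index unstable angina and early index revascularization count as MACE as worded

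*Protocol article*

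**What the plan says.** The section "Primary outcome measure" defines MACE as "the composite of cardiovascular death, new acute myocardial infarction (AMI) (type 1 or 2), unstable angina, or unexpected revascularization within 30 days". Revascularization is then specified as "any unplanned hospitalization with cardiac revascularization performed within the first 12 h after hospital admission in the context of ACS". An index rule follows for one component: an AMI found in the first 12 h after presentation, in a patient who has not left hospital, "will be considered as the index presenting AMI and not included as an endpoint event". AMI starting later, or found within that window after discharge, does count.

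Other sections that bear on the point:

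- The adjudicated final diagnosis: "Unstable angina will be diagnosed in patients with typical ischemic symptoms at rest or minor exercise with no evidence of acute myocardial necrosis". No timing relative to the index visit is given.
- Secondary outcome measures: "Incidence of ED representation or hospitalization for unstable angina within 30 days after the index presentation". This narrower wording is used only for the secondary outcome.
- Study governance: the committee evaluates "all components of the primary endpoint, including index (within 12 h of initial presentation) and subsequent MI". The split between index and subsequent events is named for MI alone.
- Population: the primary aim is stated "for patients presenting with suspected NSTE-ACS to the ED". The sample size section gives its 3% control rate for patients managed as outpatients, and the limitations section describes the primary outcome as assessed in outpatients.

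**The concern.** The endpoint is meant to measure the safety of a triage strategy. The disease a patient arrives with cannot be caused by that strategy. The protocol recognises this for AMI, but not for unstable angina or for the revascularization that treats the presenting event.

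Three things are at stake. Index events add variance to an absolute difference judged against a fixed 1.5-point margin. They push the event rate above the 3% used for planning. They also make the result depend on how index events are timed and labelled, which may differ between conditions for reasons unrelated to safety.

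**Working it through.** **Step 1. Index rule by component.**

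| Component | Rule for the presenting event |
|---|---|
| Cardiovascular death | none needed |
| AMI | excluded if found within 12 h of presentation while still in hospital |
| Unstable angina | none |
| Revascularization | none; counts if within 12 h of an unplanned admission for ACS |

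The two 12-h clocks also start at different points: index presentation for AMI, hospital admission for revascularization.

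**Step 2. Apply the wording to cases.**

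- Presents with AMI, admitted, revascularized 11 h after admission: the AMI is excluded, the revascularization counts, so the patient has MACE.
- Same patient, revascularized at 13 h: no MACE.
- Presents with unstable angina, no later event: MACE.
- Discharged, readmitted unplanned with ACS, revascularized at 13 h: the revascularization does not count. The patient may still enter the composite through new AMI or unstable angina.

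**Step 3. Which population?** If only outpatients are analysed, most index admissions drop out. But the primary outcome section states its aim for all patients with suspected NSTE-ACS and gives rules for events in hospitalized patients. The statistical analyses section states no outpatient restriction and plans specificity and positive predictive value for MACE in the rule-in group. The text does not settle the question.

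**Step 4. The plan's sample size.** Inputs (sample size section): rate 3%, margin 1.5%, one-sided 5%, power 80%, total 4260. Individually randomized non-inferiority formula:

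n per arm = (1.645 + 0.842)² × 2 × 0.03 × 0.97 / 0.015² ≈ 1600, total 3200.

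4260 is 1.33 times this. A standard stepped-wedge calculation (11 single-cluster steps, equal cells, fixed period effects, ICC 0) needs 5277, or 6397 with an excluded transition period. So 4260 is not reproduced. Without an ICC or enrolment per step it cannot be called wrong on these inputs, and the present point does not depend on it. The next step therefore takes the plan's own claim of 80% power at 3%.

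**Step 5. Effect of a higher rate (rates assumed).** The Introduction says "ACS is diagnosed only in a minority (about 5–20%, depending on the clinical setting", but no document gives the share with index unstable angina or early index revascularization. At 80% power the margin equals 1.645 + 0.842 = 2.487 standard errors, and the standard error scales with √[p(1−p)]. So

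power = Φ(2.487 × √[0.0291 / (p(1−p))] − 1.645).

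| Assumed MACE rate | √ ratio | Power at 4260 | Total N for 80% |
|---|---|---|---|
| 3% (plan) | 1.000 | 80% | 4260 |
| 5% | 0.783 | about 62% | about 6960 |
| 8% | 0.629 | about 47% | about 10780 |
| 10% | 0.569 | about 41% | about 13180 |

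**Step 6. Direction of bias.**

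- *Timing.* Suppose a share q of patients is revascularized for an index AMI and a fraction s of them crosses the 12-h line under one condition. MACE then differs by q × s with no difference in harm. With assumed q = 5% and s = 10–30%, that is 0.5–1.5 points; with q = 10%, 1.0–3.0 points. The margin is 1.5 points.
- *Labelling.* Table 1 lists no serial measurement at three Japanese hospitals under usual care. An index event called unstable angina there (counted) could be called index AMI (not counted) under 0/1-h care. That would favour the intervention.

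The two mechanisms can oppose each other, and the documents do not allow a net figure.

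**The case against.** The strongest reply is that index events were never meant to count. The words unexpected and unplanned suggest a later admission. The 3% rate sits below the 5–20% ACS share and is stated for outpatients. Any revascularization within 30 days is already a secondary outcome, and a blinded committee adjudicates every component, probably under a charter that is not shown. This stands as evidence of intent. It does not change the definition: the current wording admits index events, the only index rule written is for AMI, and the outpatient wording conflicts with the primary outcome section. Nor does an outpatient reading remove the 12-h cut-off at readmission.

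Two stronger readings are tempting and are not supported:

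- *That the endpoint penalises faster treatment.* This requires the algorithm to shorten the interval from admission to revascularization, or admission to mean ED arrival. If admission means ward admission, quicker triage could move both times together. The discussion of Asian characteristics says only that the algorithm could aid rapid transfer to specialist facilities, whereas the trial hospitals already offer advanced interventional therapy. Labelling of unstable angina may push the other way.
- *That the 3% rate cannot hold.* It is an outpatient rate, and the ACS share refers to ED chest-pain patients generally. In the full population with index events counted, 3% is unlikely, but it is not shown to be impossible.

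**Conclusion.** The point holds as a defect in the definition. Followed literally, it counts index unstable angina and early index revascularization as MACE, excludes the index AMI being treated, and omits revascularization beyond 12 h of a later readmission. The analysis population that would limit the damage is described inconsistently.

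The size is not known from the documents. The power figures (about 62% at 5% MACE, 47% at 8%) assume those rates and take the plan's 80% at 3% as given. The timing figures assume both the share revascularized and the shift. They show that plausible amounts of index counting could matter against a 1.5-point margin, not that they have. The direction of any bias is uncertain. If index events are excluded, the 3% assumption can stand and this point leaves the planned 4260 and 80% unchanged.

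**What to change.** 1. State the primary analysis population once, and bring the primary outcome, sample size, statistical analyses and limitations sections into line with it.
2. Count unstable angina and unplanned revascularization only if they occur after index discharge, or are adjudicated as a new episode outside the index 12-h window, parallel to the AMI rule.
3. Remove the condition of 12 h after hospital admission for readmissions.
4. Report index-admission revascularization separately. The data already fall within the secondary outcome of any revascularization within 30 days.
5. Extend the index/subsequent split in the study governance section to all ischaemic components.

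**Cost.** This changes components of the primary endpoint, so it needs a protocol amendment with ethics approval and a registry update (Protocol amendment section). With 2124 patients included by the status date, some adjudicated events would need re-classification. The existing committee can do this blinded and before analysis. No additional patients are needed for this change.

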#### Secondary outcome measures

The following predefined secondary outcomes are considered:The proportion of patients managed as outpatients in order to quantify the efficacy of the investigated approaches in both arms.The time from ED presentation to discharge in outpatients. The ED dwell time is derived from a common electronic patient record system used across all participating sites and is calculated as the time of the medical examination between the start time (sign-in time: defined as first medical contact with a MD or the triage nurse) and the end time (sign-off time: defined as the time when the attending physician has finished all medical procedures in the ED, including charting, with the patient to ready to leave the examination room either to be discharged or transferred to a different unit/ward within the hospital).All-cause mortality (cardiovascular death and non-cardiovascular death) and new myocardial infarction (type 1 or 2) within 30 days after the index presentation.Incidence of any cardiac revascularization within 30 days after the index presentation.Incidence of ED representation or hospitalization for unstable angina within 30 days after the index presentation.Costs for healthcare resource use within 30 days following the index ED presentation are calculated based on each country’s guidelines and cost tables for hospitals. Different costs are used for academic and general hospitals. For each patient, the costs are calculated based on the observed number and type of healthcare resources used.Incidence of cardiac examinations (e.g., stress testing or coronary angiography) within 30 days after the index presentation. Adherence to the intervention condition (the 0/1-h algorithm) was evaluated.

### Study design and population (Fig. 1)

This is a prospective, international randomized trial involving eleven hospitals (*Japan*; Juntendo University Nerima Hospital, Juntendo University Urayasu Hospital, Sakakibara Heart Institute, Shimada general hospital, Teikyo University School of Medicine, Yokohama Rosai Hospital, *Singapore*; National Heart Centre Singapore and Sengkang General Hospital, *Thailand*; Maharaj Nakorn Chiangmai Hospital, *Taiwan*; Taipei City Hospital Yangming Branch, *Malaysia*; University Teknologi MARA Teaching Hospital, Kuala Lumpur Hospital, and Institute Jantung Negera) from five Asian countries. These hospitals provide advanced interventional therapy to patients presenting with suspected ACS. Patients of ≥18 years of age who presented to the ED of participating hospitals with symptoms suggestive of NSTE-ACS (e.g., chest pain, epigastric pain, radiating pain to the neck or shoulder, shortness of breath) are eligible for enrollment in the DROP-Asian ACS study, if the onset of symptoms occurred within the last 12 h. Patients were excluded from the present study if they presented with ST elevation myocardial infarction, cardiogenic shock, on chronic hemodialysis, or chest pain following chest trauma, or if they were unwilling or unable to provide their informed consent. All participating patients or their legally authorized representatives will provide written informed consent. This study is conducted according to the principles of the Declaration of Helsinki. Ethical approval has been received from the local ethics committees. This study is registered in the Japanese Trial Registry (Reg. No. UMIN ID; UMIN000042461; https://upload.umin.ac.jp/cgi-openbin/ctr_e/ctr_view.cgi?recptno=R000048466).

